## 13 **DATA MANAGEMENT**

### 13.1 **DEFINITION OF SOURCE DATA**

All evaluations that are reported in the electronic Case Report Form (eCRF) must be supported by appropriately signed identified source documentation related.

### 13.2 **SOURCE DOCUMENT REQUIREMENTS**

According to the guidelines on GCP, the Monitoring Team must check the CRF / eCRF entries against the source documents, except for the pre-identified source, data directly recorded/enclosed in/to the Case Report Form. The Informed Consent Form will include a statement by which the subject allows the Sponsor's duly authorized personnel and the regulatory authorities to have direct access to source data which supports the data on the Case Report Forms (e.g. subject's medical file, appointment books, original laboratory records, etc.). These personnel, bound by professional secrecy, will not disclose any personal identity or personal medical information.

### 13.3 **USE AND COMPLETION OF CASE REPORT FORMS (CRFS) AND ADDITIONAL REQUEST**

#### 13.3.1 **Data collection**

All clinical data will be reported electronically by the Investigator or authorized designee on a web-based electronic Case Report Form (eCRF). This eCRF is specifically designed for the study and developed by the Data Management Department of Eurofins Optimed using LifeSphere EDC® 5.0.2. or higher, a validated Electronic Records/Electronic Signature-compliant (21 CFR Part 11) application.

Should a correction be made, the corrected information will be entered in the eCRF and the initial information will be tracked in the audit trail.

#### 13.3.2 **Responsibilities**

The Investigator or authorized designee is responsible for the timeliness, completeness, and accuracy of all observations and other data pertinent to the clinical investigation in the eCRFs. The Investigator will ensure that all data are entered promptly (within 4 days) after the evaluation has occurred, in accordance with source documents and specific instructions accompanying the eCRFs, designed specifically for the study. The Data Management Department of Eurofins Optimed will provide all tools, instructions, and training necessary to complete the eCRF, and each user will be issued a unique username and password. The data management of Eurofins Optimed will be responsible for data processing, in accordance with the CRO data management procedures.

|                                                                                   |                    |                                                                      |
|-----------------------------------------------------------------------------------|--------------------|----------------------------------------------------------------------|
| [figure not shown] | DOCUMENT    | Protocol ID : MPOH05
EudraCT N° : 2019-004253-89
Version: 10.0 |
|                                                                                   | CIMON STUDY | Date : 04 MAY 2021
Page 51 / 70                                   |

### **13.4 DATA MANAGEMENT**

During the study, through regular data collection and monitoring, clinical data reported in the eCRFs will be integrated into the clinical database. Computerized logic and/or consistency checks will be systematically applied in order to detect errors or omissions. Queries will be generated and submitted through the electronic data capture (EDC) system to the investigator sites for resolution (queries should be answered within 10 days). Correction will be made either automatically from the immediate completion or following the review of the data during the Eurofins Optimed monitoring. An audit trail, which will be initiated at the time of the first data entry, allows tracking all modifications. The Data Management Department of Eurofins Optimed may generate additional requests to which the Investigator must respond electronically by confirming or modifying the data questioned. The requests with their responses will be implemented to the eCRFs. Each step of this process will be monitored through the implementation of individual passwords and regular backups to maintain appropriate database access and to ensure database integrity. When eCRFs are complete and all queries have been answered, the Investigator has to sign the eCRFs. Then eCRFs are locked and no modification is possible anymore. After integration of all corrections in the complete set of data, the database will be locked and saved before being released for statistical analysis. After database lock, a Patient Data Report (PDR) that consists of the printing out an entire casebook for a subject will be generated for each subject in .pdf format. PDRs are sent to site and sponsor via secured exchange platform.

|                                                                                   |                    |                                                                      |
|-----------------------------------------------------------------------------------|--------------------|----------------------------------------------------------------------|
| [figure not shown] | DOCUMENT    | Protocol ID : MPOH05
EudraCT N° : 2019-004253-89
Version: 10.0 |
|                                                                                   | CIMON STUDY | Date : 04 MAY 2021
Page 52 / 70                                   |

## 14 **STATISTICAL CONSIDERATIONS**

The material of this section is the basis of the Statistical Analysis Plan for the study. This plan may be revised during the study to accommodate Clinical Trial Amendment and to make change to adapt unexpected issue in study execution and data that affect planned analyses. These revisions will be based on review of the study and data, and a final plan will be issued before database lock.

### 14.1 **GENERAL CONSIDERATIONS**

This is a single arm multicenter study aiming at evaluating the safety of a freeze dried, full ecosystem, encapsulated full-ecosystem, intestinal microbiota biotherapeutic product (MaaT033).

#### 14.1.1 **Endpoints**

Detailed definitions of endpoints are given in [section 8.3.1](#).

The primary evaluation criterion is the proportion of patients having experienced drug related adverse events for the determination of a recommended phase 2 dose (RP2D).

Secondary endpoints are:

- Evaluation of microbiota reconstitution post MaaT033
  - Alpha-diversity: Simpson index, Shannon index, Richness index
  - Similarities between samples: Bray-Curtis/Jaccard/UniFrac distances indexes, Sorensen index, Pearson index, Spearman index
- Duration of overall response on the hematologic malignancy (blasts)
- Compliance to allogeneic MaaT033 treatment
- Acceptability of MaaT033 by the patient
- Number of patients receiving the full treatments
- Evaluation of MaaT033 activity and/or impact on:
  - Number and percentage of patients having experienced at least one infection requiring antibiotic/antiviral/antifungal therapy after MaaT033 treatment start
  - Number and percentage of patients having experienced at least one microbiologically documented infection requiring antibiotic/antiviral/antifungal therapy after MaaT033 treatment start
  - Events potentially related to GI infection (fever, diarrhea, abdominal pain, bloating)
  - Fecal resistome and MDRB carriage
  - Evaluation of stools: Bristol stool chart

Exploratory endpoints encompass

- Assessment of a microbiota signature
- Impact of MaaT033 on the immune system

The final main analysis will be performed when all enrolled patients have completed treatment and follow-up period (28 days). Complementary analysis on safety and 12 months' survival follow up will be updated when all patients have had the opportunity to be followed for 12 months.

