|                                                   | 
After recovering from neutropenia (neutropenia is defined as Poly-Nuclear Neutrophils count <math>\leq 0.5 \times 10^9</math> cells/L)
 
Dose regimen:
 
 
- Cohort 1 (3 patients): 1 capsule (per os) at day1 and at day7, e.g., on a Tuesday and the Monday of the following week. Step up of dose regimen will then be as follows:
 
- Cohort 2 (6 patients): 1 capsule/day (corresponding to a maximum of 7 capsules) – 7 days (period of treatment)
 
- Cohort 3 (6 patients): 3 capsules/day (corresponding to a maximum of 21 capsules) – 7 days
 
- Cohort 4 (6patients): 3 capsules/day (corresponding to a maximum of 42 capsules) – 14 days
 
- 9 capsules/day (corresponding to a maximum of 63 capsules) – 7 days
 
 |
| ASSESSMENT/
SCHEDULE                   | 
Estimated inclusion period: 5 to 7 months
 
Calculated total duration of the study from start to last patient last visit: 7 to 9 months
                                                                                                                                                                                                                                                                                                                                                                                                                                                                                                                                                                                                                                                                         |

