**V1: Start of the treatment (day1) - End of induction neutropenia**

**V2: Safety interim visit (day7 +/-2) - Clinical assessment visit**

**V3: Cycle start (day 19 +/- 5days)**

**V4: End of the study (day44 +/-10days) = End of cycle**

|                                                                                   |                    |                                                                      |
|-----------------------------------------------------------------------------------|--------------------|----------------------------------------------------------------------|
| [figure not shown] | DOCUMENT    | Protocol ID : MPOH05
EudraCT N° : 2019-004253-89
Version: 10.0 |
|                                                                                   | CIMON STUDY | Date : 04 MAY 2021
Page 15 / 70                                   |

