#### 11.1.7 End of study, Visit 4 - D44 post-inclusion - Cycle STOP

This visit will be performed 44 days (+/-10days) after the MaaT033 treatment start.

During this visit:

- The physician will proceed to a physical exam including collection of vital signs and clinical evaluation
- Blood samples (30mL) and fecal swabs will be collected (See Table 1 for analysis details)
- Evaluation of treatment tolerability, acceptability, compliance and safety

Nasopharyngeal (or any other validated methods: salivary test, oro-pharyngeal test or other) and fecal SARS-CoV-2 tests will be performed.

During this visit, the patient will report to the physician any adverse reaction or severe event occurred since the previous visit. All AE and SAE must be reported in the eCRF.

After V4, patient will be followed like any AML or HR-MDS patient.

In total, 120mL of blood will be collected for each patient during the study.

|                                                                                   |                    |                                                                      |
|-----------------------------------------------------------------------------------|--------------------|----------------------------------------------------------------------|
| [figure not shown] | DOCUMENT    | Protocol ID : MPOH05
EudraCT N° : 2019-004253-89
Version: 10.0 |
|                                                                                   | CIMON STUDY | Date : 04 MAY 2021
Page 38 / 70                                   |

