## 14.3 STATISTICAL METHODS

### 14.3.1 Planned analyses

One primary analysis is planned after the completion of the last patient last visit (LPLV)

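### Section 14.1.1 triggers the final analysis at a 28-day follow-up found nowhere in the visit schedule, and announces a 12-month survival update for which no survival data are planned

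*Protocol*

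**What the plan says.** Section 14.1.1 gives the timing of the main analysis: "The final main analysis will be performed when all enrolled patients have completed treatment and follow-up period (28 days". It then adds a complementary analysis of safety and survival: "12 months' survival follow up will be updated when all patients have had the opportunity to be followed for 12 months". Among its secondary endpoints it lists "Duration of overall response on the hematologic malignancy (blasts".

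Other sections describe a different end point for follow-up and analysis:

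- Section 14.3.1: "One primary analysis is planned after the completion of the last patient last visit (LPLV".
- Section 4 (flow chart notes): "V4: End of the study (day44 +/-10days) = End of cycle". Section 11.1.7 anchors this visit at 44 days, give or take 10, after treatment start.
- Section 14.3.5 describes adverse events between V1 and V4.
- Section 11.1.7, on what follows the last visit: "After V4, patient will be followed like any AML or HR-MDS patient".
- Synopsis (section 3): "Calculated total duration of the study from start to last patient last visit: 7 to 9 months", with inclusion estimated at 5 to 7 months and participation of up to 6-7 weeks per patient.
- Section 11.4.2 mentions survival monitoring only to day 44, and only for patients who stop treatment because of deterioration or progression.

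**The concern.** A protocol should have one rule for when the main analysis is run, and that rule should fall after the data it needs have been collected. Here there are two rules, and the one in section 14.1.1 uses a period that does not appear in the flow chart notes, section 8.2.1, Table 1 or section 11.1.7. If it fires before V4 is complete, the V1-to-V4 safety summary in 14.3.5 and the V4 engraftment assessment in 8.3.2 would be incomplete for some patients.

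The survival update is a separate difficulty. It promises a result at 12 months in a trial whose scheduled observation ends after about six weeks. Section 14 describes itself as the basis of the statistical analysis plan, so both statements are liable to be carried forward.

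**Working it through.** **1. The plan's own study length.** Inputs are inclusion of 5 to 7 months (synopsis) and V4 at day 44, latest 44 + 10 = day 54 (section 11.1.7). At 30.44 days per month:

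- 5 months of inclusion: 5 + 44/30.44 = 6.4; 5 + 54/30.44 = 6.8 months.
- 7 months of inclusion: 7 + 44/30.44 = 8.4; 7 + 54/30.44 = 8.8 months.

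Rounded up, these give the stated 7 to 9 months. The published duration is therefore built on follow-up ending at V4.

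**2. Where 28 days falls.** The V4 window is 44 − 10 = D34 to 44 + 10 = D54. Treatment lasts 7 or 14 days (section 11.4.3).

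| Reading of the 28 days | Day | Distance to nominal V4 (D44) | Relation to V4 window |
|---|---|---|---|
| From treatment start | 28 | 44 − 28 = 16 days before | 34 − 28 = 6 days before it opens |
| After a 7-day regimen | 7 + 28 = 35 | 44 − 35 = 9 days before | inside |
| After the 14-day regimen | 14 + 28 = 42 | 44 − 42 = 2 days before | inside |

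The nominal interval from V3 (D19) to V4 is 44 − 19 = 25 days, so that does not explain the figure either. Section 14.1.1 does not say from which day the 28 days are counted.

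**3. Who could be affected.** The trigger requires all enrolled patients to have reached the point, so earlier patients will normally be past V4. Under sections 8.2.2 and 12.1.4.2, cohort 5 opens only after cohort 4 has completed V3, nominally D19. When the first cohort-5 patient is 28 days in, cohort 4 is therefore nominally at 19 + 28 = D47 or later, past nominal V4. On the nominal schedule the exposure lies mainly in the last cohort: 6 of 27 patients if escalation completes.

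**4. What is not affected.** The limiting-toxicity window runs from V1 to V3, and V3 closes at 19 + 5 = D24. On the stated windows this precedes every reading of the trigger.

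**5. The 12-month update.** Following the last patient for 12 months needs 5 + 12 = 17 to 7 + 12 = 19 months in total, against 7 to 9 stated. Nominal participation is 44/7 = 6.3 weeks, in line with the stated 6-7 weeks. Table 1 has no contact after V4, survival is not among the listed endpoints, and section 8.2.1 ends adverse-event collection at V4.

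**6. Duration of response.** It is in the secondary list of section 14.1.1 but not in section 8.3.2. Section 8.3.1, to which 14.1.1 refers for definitions, does not define it. Section 11.2 does provide for response to be evaluated at inclusion and throughout the study, so response status is available up to V4.

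**The case against.** The best defence of the trigger is that treatment plus a 28-day follow-up is the natural reading. It gives D35 or D42, both inside the V4 window. Section 14.3.1 requires the last visit, 14.3.5 requires data to V4, and section 13.4 requires completed case report forms and a database lock before analysis. An early cut would happen only if one sentence overrode all of these. That is fair: it makes this half a conflict of definition more than a likely loss of data. It does not remove the conflict, because the protocol states no such anchor and both D35 and D42 still fall short of nominal V4.

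Three stronger readings are tempting and are not supported.

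- A reader might infer that nothing at all is collected after V4. Sections 12.1.3.9 and 12.1.3.10 provide for continued follow-up of serious adverse events, reporting of later related ones, and follow-up of pregnancy to outcome. What is missing is scheduled collection and survival follow-up; the safety part of the complementary analysis is not wholly without data.
- A reader might infer that 16 of 44 days (36%) of the trial's safety window would be lost. That treats a trigger as a cut applied to every patient, and it needs the count to start at treatment start. Nor need all those days lie in a chemotherapy cycle, since section 8.2.1 allows for patients who start no new cycle.
- A reader might infer that nearly all response durations would be censored at V4. The protocol gives no relapse rate from which to say so. It can be said only that a response still ongoing at V4 has no scheduled observation beyond D54.

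**Conclusion.** The point holds. Section 14.1.1 contradicts section 14.3.1, the V4 end of study and the V1-to-V4 window of section 14.3.5. Depending on the anchor, its trigger is 16, 9 or 2 days before nominal V4; only the first precedes the whole V4 window. The possible consequence is missing V4 safety and engraftment data in the last-enrolled patients, mainly the last cohort, assuming cohorts run in sequence on nominal visit days. The limiting-toxicity assessment is not at risk on the stated windows.

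The survival half has no reconciling reading: no scheduled data exist, and the study would have to run about 10 months longer than stated (17 − 7, or 19 − 9). Whether the sponsor intended a longer follow-up or left the sentence in by oversight cannot be told from the protocol. The mismatch on duration of response is a smaller inconsistency between two endpoint lists.

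**What to change.** - **Trigger.** Replace the 28-day sentence in section 14.1.1 with one rule consistent with 14.3.1: the final main analysis is performed after the last patient has completed V4 (LPLV) and the database has been locked.
- **12-month survival.** Delete the update. If it is intended, add scheduled vital-status collection after V4, make sure consent covers it, and restate participation per patient and total study duration.
- **Duration of response.** Align the secondary list in 14.1.1 with section 8.3.2, and describe response status over V1 to V4, because scheduled follow-up ends by D54.

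Stating one trigger, deleting the update and aligning the lists cost wording only, because no scheduled data collection is given up. Keeping the survival analysis costs about 10 further months, plus the added collection and an amendment.

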#### 14.1.2 **Handling of missing data**

Missing data will not be replaced.

|                                                                                   |                    |                                                                      |
|-----------------------------------------------------------------------------------|--------------------|----------------------------------------------------------------------|
| [figure not shown] | DOCUMENT    | Protocol ID : MPOH05
EudraCT N° : 2019-004253-89
Version: 10.0 |
|                                                                                   | CIMON STUDY | Date : 04 MAY 2021
Page 53 / 70                                   |

### 14.1.3 Type 1 error

The analysis will mainly be descriptive. The 1 error rate will be set at 0.05 and therefore two-sided 95% confidence intervals will be calculated.

## 14.2 ANALYSIS POPULATIONS

- Screened patients: all patients having signed an informed consent form
- Enrolled patients: all patients having been enrolled at V1
- Intent to treat (ITT) population: enrolled patients
- Treated patients: all enrolled patients having undergone at least one capsule intake (safety set)
- Per protocol (PP) population: all patients belonging to the ITT population with at least 60% of treatment and completion of V1, V2 and V3, with no major protocol violations (PP set)

## 14.3 STATISTICAL METHODS

### 14.3.1 Planned analyses

One primary analysis is planned after the completion of the last patient last visit (LPLV)

### 14.3.2 Descriptive statistics

Continuous variables will be described by the mean, standard deviation, minimum and maximum values, median, first and third quartiles. Categorical variables will be described by the number and percentage of each modality.

### 14.3.3 Demographics and medical history

Demographic data will be described appropriately. Medical history will be coded using the last version of the MedDRA dictionary and will be described according to the system organ and preferred term. Underlying hematologic malignancy will be described. The analysis will be conducted in the safety set.

### 14.3.4 Treatment exposure

Exposure to MaaT033 will be described by the number of capsules taken by each patient (categorical variable). Concomitant treatments will be coded with the last version of the WHODRUGS dictionary (WHO-DD) and described according to the ATC code and the drug name or preferred terms. The analysis will be conducted in the safety set.

### 14.3.5 Analysis of the main criterion

The number and percentage of patients having experienced AEs between V1 and V4 will be described. Relation of AEs to the drug treatment will be assessed by the safety committee in a final review. The committee will then provide a conclusive decision on MaaT033 safety.

|                                                                                   |                    |                                                                      |
|-----------------------------------------------------------------------------------|--------------------|----------------------------------------------------------------------|
| [figure not shown] | DOCUMENT    | Protocol ID : MPOH05
EudraCT N° : 2019-004253-89
Version: 10.0 |
|                                                                                   | CIMON STUDY | Date : 04 MAY 2021
Page 54 / 70                                   |

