#### 8.2.2 **Decision rules for choice of dose regimen**

This study has for objective to assess MTD and MAD in term of MaaT033 activity (bacteria engraftment). Activity assessment requires a minimum of 6 patients to allow for a sufficient robust analysis of engraftment.

Activity and tolerability assessment may depend both on duration of treatment and/or daily dose. Therefore, the study will assess both 7 days and 14 days dose regimen, for the 3 capsules/day dosing.

Therefore, the study will ensure that a minimum of 6 patients is included for all the dose regimen that do not reach the MTD.

Definitions:

**Minimal Active Dose (MAD):** Minimum dose regimen that will lead to a minimal activity (1 or 2, cf chapter 8.3.2) of the product.

|                                                                                   |                    |                                                                      |
|-----------------------------------------------------------------------------------|--------------------|----------------------------------------------------------------------|
| [figure not shown] | DOCUMENT    | Protocol ID : MPOH05
EudraCT N° : 2019-004253-89
Version: 10.0 |
|                                                                                   | CIMON STUDY | Date : 04 MAY 2021
Page 24 / 70                                   |

**Dose Limiting Toxicity (DLT):** Toxicity event will be defined as any related adverse event grade >3 based on CTCAE v5.0 criteria for:

- Blood and lymphatic system disorders (DLT when grade4 or 5)
- Immune system disorders (DLT when grade4 or 5)

And any related adverse event grade  $\geq 3$  for all other system organ.

**Maximal Tolerated Dose (MTD):** Maximal dose for which only 0 or 1 patient do experience limiting toxicity out of a cohort of 6 patients.

The study has an adapted “6 dose titration” escalation design to allow for assessment of tolerability (research of the Maximal Tolerated Dose) and of activity (research of Minimal Active Dose):

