#### **8.3.1 Primary endpoint: MaaT033 tolerability**

Occurrence of MaaT033 limiting toxicity-related treatment emergent (serious) adverse events, grade $\geq$ 3, from treatment start (visit 1) to the next cycle (visit 3). AE and SAE relationship will be validated by a final safety committee. Cf safety description § section 12. All adverse events will be categorized according to the CTCAE v5.0 criteria.

Tolerability assessment will be done with the evaluation of LTD. Based on the MTD and MAD evaluated in the different cohorts, the best dose regimen in terms of activity might be re-evaluated. Therefore, the minimal dose that is safe and active will support the best dose regimen that may need to be adjusted correspondingly.

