#### **12.1.4.1 Tolerability consideration:**

Investigators will be trained regarding the mode of action of the investigational medicinal product and to be particularly attentive to any signs of toxicity.

**Dose Limiting Toxicity (DLT):** Based on the literature and our preclinical data, no particular toxicity is expected. Toxicity events will be defined as any at least possibly related adverse event grade  $\geq 3$  based on CTCAE v5.0 criteria. Due to the specific therapeutic protocol that blood cancer patients usually follow, the follow-up of patients in term of DLT is set from V1 (end of neutropenia) to V3 (start of a new chemotherapy cycle, or consolidation). Nevertheless, there are some anatomical or physiological system events that will be considered as expected in the context of patients with AML or HR-MSD, and thus not related to the treatment. Such events will only be considered DLT when grade  $> 3$ :

- Blood and lymphatic system disorders (DLT when grade 4 or 5)
- Immune system disorders (DLT when grade 4 or 5)

Depending on the number of DLTs, the dose is either escalated (0 DLTs) or de-escalated ( $\geq 2$  DLTs). Due to our specific drug activity assessment goals, cohorts 2 to 5 will systematically be expanded with 3 extra patients (0 or 1 DLTs) each.

|                                                                                   |                    |                                                                      |
|-----------------------------------------------------------------------------------|--------------------|----------------------------------------------------------------------|
| [figure not shown] | DOCUMENT    | Protocol ID : MPOH05
EudraCT N° : 2019-004253-89
Version: 10.0 |
|                                                                                   | CIMON STUDY | Date : 04 MAY 2021
Page 49 / 70                                   |

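### Section 14.3.5 analyses any adverse event from V1 to V4, but the declared primary endpoint is limiting toxicity of grade 3 or above from V1 to V3

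*Protocol*

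**What the plan says.** Section 8.3.1, repeated in the synopsis, defines the primary endpoint as "Occurrence of MaaT033 limiting toxicity-related treatment emergent (serious) adverse events" of grade 3 or above, "from treatment start (visit 1) to the next cycle (visit 3". A safety committee validates the relationship to treatment.

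Section 8.2.2 defines a DLT as a related event of grade 3 or above. Two organ systems have a higher threshold: "Blood and lymphatic system disorders (DLT when grade4 or 5", and likewise immune system disorders. It defines the MTD as "Maximal dose for which only 0 or 1 patient do experience limiting toxicity out of a cohort of 6 patients". Section 12.1.4.1 states that "the follow-up of patients in term of DLT is set from V1 (end of neutropenia) to V3", the start of the next chemotherapy cycle or consolidation, and gives the patients' treatment protocol as the reason.

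Section 8.3.2 makes overall safety, covering all adverse events from V1 to V4, part of the secondary evaluation.

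In the statistical chapter, section 14.1.1 points to 8.3.1 for detailed definitions and then summarises: "The primary evaluation criterion is the proportion of patients having experienced drug related adverse events". Section 14.3.5 then specifies the analysis: "The number and percentage of patients having experienced AEs between V1 and V4 will be described". It goes on: "Relation of AEs to the drug treatment will be assessed by the safety committee in a final review", after which the committee gives its decision on safety.

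**The concern.** The section that carries the primary analysis does not analyse the primary endpoint. It differs in the kind of event, in grade and in window, and the relatedness assessment is not made a condition of the count. What it describes is the secondary overall-safety summary. No other part of chapter 14 specifies an analysis of DLTs from V1 to V3.

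At stake is what the study reports as its main result. Chapter 14 calls itself the basis of the statistical analysis plan. A plan that follows 14.3.5 inherits the mismatch, and one that follows 8.3.1 contradicts 14.3.5. The study is open-label, so leaving the choice until events are known would allow it to depend on the data.

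**Working it through.** This is mainly a comparison of text. The plan gives no figure of its own on this point to reproduce.

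| Place | Event counted | Grade | Relatedness | Window |
|---|---|---|---|---|
| 8.3.1 and synopsis (primary endpoint) | limiting-toxicity-related, treatment-emergent | 3 or above | validated by committee | V1 to V3 |
| 8.2.2 (DLT) | adverse event | 3 or above; 4 or 5 for two organ systems | related | cohort reviewed after V3 |
| 12.1.4.1 (DLT) | adverse event | as 8.2.2 | at least possibly related | V1 to V3 |
| 14.1.1 (summary) | drug-related adverse event, referring to 8.3.1 | not stated | drug related | not stated |
| 14.3.5 (analysis of main criterion) | adverse event | not stated | assessed by committee, but not a limit on the count | V1 to V4 |
| 8.3.2 (secondary, overall safety) | all adverse events | not stated | evaluated by committee | V1 to V4 |

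The 14.3.5 row agrees with the secondary row and not with the primary one.

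**Size of the added window.** Inputs from the flow chart in section 4: V1 at day 1, V3 at day 19 ± 5, V4 at day 44 ± 10. Share of the 14.3.5 window lying after V3 = (V4 − V3) / (V4 − V1).

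- Nominal: (44 − 19) / (44 − 1) = 25/43 = 58%.
- Smallest (V3 at day 24, V4 at day 34): 10/33 = 30%.
- Largest (V3 at day 14, V4 at day 54): 40/53 = 75%.

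Section 8.2.1 says a new chemotherapy cycle follows V3 only if one is given. The added interval is therefore a chemotherapy cycle for some patients and untreated follow-up for others.

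**What the declared endpoint would show.** With the exact (Clopper-Pearson) two-sided 95% interval, a cohort with 0 of 6 DLTs gives 0% to 45.9%, and 1 of 6 gives 0.4% to 64.1%. These are the two outcomes compatible with the MTD definition.

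**The case against.** Several points on the other side are sound.

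- **Escalation does not use this percentage.** A reader might infer that the MTD or patient protection is compromised. The documents do not support that. Sections 8.2.2 and 12.1.4 set escalation and the MTD by DLT counts at cohort reviews, and the committee selects the phase 2 dose (12.1.4.3). The defect is confined to the reported primary analysis.
- **Section 14.1.1 is not clearly a rival endpoint.** It refers back to 8.3.1 and states no grade. Its summary sentence is loose and should be aligned, but it need not be read as meaning events of any grade.
- **Causality is not ignored.** Section 14.3.5 includes committee review of relatedness. That review does not restrict the percentage and supplies no grade, DLT definition or V3 cut-off, so the mismatch stands.
- **The absence of a split by regimen is only silence**, of the kind an analysis plan commonly fills. It is not an error in itself.
- **The data can be recovered.** DLTs up to V3 are a subset of the events collected, and chapter 14 allows revision before database lock.

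A reader might also infer that the any-event percentage would sit at its ceiling in every cohort and so could not separate regimens. The protocol gives no adverse-event rate. As an illustration with assumed per-patient rates, P(at least 2 of 6) = 1 − (1 − p)^6 − 6p(1 − p)^5. This is 0.033, 0.114 and 0.345 at p = 5%, 10% and 20%, against 0.998 and 1.000 at 80% and 90%. It shows that the two measures can behave very differently. It does not show what this trial would observe, and nothing in the protocol applies the 2-of-6 rule to the 14.3.5 count.

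**Conclusion.** Wrong as written. Section 14.3.5 fixes a main analysis that departs from the primary endpoint in 8.3.1 and the synopsis in event type, grade and window, and that leaves relatedness off the count. It duplicates the secondary overall-safety evaluation. The added V3 to V4 interval is nominally 58% of the counted time, and 30% to 75% if visits fall at the edges of their windows. That range assumes visits are held within the stated windows, and the interval contains chemotherapy only for patients who start another cycle. The contradiction itself rests on the text alone and needs no assumed event rate. Dose escalation, the MTD and data collection are not affected.

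**What to change.** Rewrite 14.3.5 so that the main criterion is the number and percentage of treated patients with at least one committee-adjudicated DLT from V1 to V3. Present it by dose regimen, with the two-sided 95% confidence interval already planned in 14.1.3. Report all adverse events from V1 to V4 under overall safety, which 14.1.1 does not currently list among its secondary endpoints, and align the summary sentence in 14.1.1.

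Before database lock, reconcile the DLT wording to one definition, a choice that belongs to the sponsor and the safety committee:

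- 8.2.2 says related, while 12.1.4.1 says at least possibly related.
- 8.3.1 gives grade 3 or above without the organ-system exception found in 8.2.2 and 12.1.4.1.
- For cohort 1, 12.1.4.2 reviews DLTs between V1 and V2, while 8.2.2 waits for V3.

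The cost is wording in the protocol and in any analysis plan. Events, grades and causality are already recorded under section 12.1.3.5, so no new data are needed.
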